**Purpose of the project:**

The aims of this study are to investigate the effects of dry needling (DN) with ultrasound (US)-guided and with placebo US-guided real-time US imaging on patients with knee osteoarthritis (KOA). Control group will be used to compare the effects of routine exercise therapy. The findings obtained from this study will help to improve the efficient in applying DN technique to KOA patients.

**The type of research project:**

This is a double-blind randomized controlled trial.

**The location where the project is going to be conducted:**

All procedures will be conducted at the laboratory of Caritas Institute of Higher Education.

**Funding agency and grant number**:

This study is funded by the grant from the Caritas Institute of Higher Education for publication with reference code: IDG200101.

**Background:**

Nowadays, aging population is the world-wide facing problem (WHO, 2018) and KOA is the most common type of osteoarthritis (OA) in aging population (Andrianakos et al., 2003). Its prevalence is rising along with the increasing aging population (Felson et al., 2000). Pain and dysfunction are the two main clinical symptoms. Pain (Naredo et al., 2005; Rathwa, Prajapati, & Deepak, 2019; Roos & Toksvig-Larsen, 2003) impaired muscular stabilization (Brandt et al., 2000; Cowan, Bennell, Hodges, Crossley, & McConnell, 2001), reduced range of motion (Steultjens, Dekker, van Baar, Oostendorp, & Bijlsma, 2000), and functional disability (Granvir, 2015; Harkey et al., 2019; Rathwa et al., 2019; Sadatsuki et al., 2019).

More recently, DN has been used in treating musculoskeletal pain with success. The technique of DN involves needle insertion into the target (in most condition, the most painful site) sites, then repeated puncture aiming to stimulate an inflammatory healing response. The needling may disrupt the collagen fibres at the target structure that may cause local haemorrhage and such micro-inflammation may lead to granulation tissue formation and enhanced tendon strength (Davidson & Jayaraman, 2011).

US imaging has been used as a guided intervention including DN treatment that passing the needle repeatedly through the abnormal tendon substance for a period of time (Daftary & Karnik, 2015; James et al., 2007, Lungu et al., 2018). The selection of needling site is based on anatomical lesion, and manual manipulation will be applied to the needles repeatedly in DN. The advantage of US imaging obviously allows more histological and radiological of the processes involved in soft-tissue injury that leads to novel targeted treatment (Davidson & Jayaraman, 2011). US-guided DN has been investigated and showed improvement in the efficacy of management such as rotator cuff tendinopathy (Fabbro et al., 2012), chronic Achilles tendinopathy (Yeo, Kendall & Jayaraman, 2016) and patellar tendinopathy (Colberg & Henderson, 2017) which allows more precise location to the target anatomical structures; and let the therapists to understand more about the current condition of the target structures (Lindseth et al., 2013; Mcnally, 2011).

To the best of my knowledge, there is no study in the literature that researches the impact of DN with and without US-guidance on pain management and functional recovery in patients presenting with KOA. The current study will include a control group to contrast the condition of natural healing with routine exercise and knee care against the interventions of DN with and without US guidance. An effective physiotherapy for patients with KOA has been recommended at least 4 sessions of weekly treatment (Vaishya et al. 2016).

**Null hypotheses:**

There are two null hypotheses to be tested in this study:

Null hypothesis 1: There would be no significant differences on pain modulation among the subject groups receiving US-guided DN (G1), placebo US-guided DN group (G2) and the control (G3).

Null hypothesis 2: There would be no significant difference on modulation on functional scores among the subject groups receiving US-guided DN (G1) compared to those in the placebo US-guided DN group (G2) or the control group (G3).

**Outcomes measures:**

Primary outcomes:

1. Pain level of the KOA patients will be assessed by Visual-Analogue Scale (VAS) (Alghadir et al., 2018; Boonstra et al., 2008)
2. The functional mobility of the KOA patients will be assessed by the Knee Injury and Osteoarthritis Outcome Score (KOOS)-short form (Roos et al., 2003; Cheung, Ngai and Ho., 2016)

Secondary outcomes:

1. Compliance of Exercise

Exercise compliance for participants was assessed at 4 weeks and 8 weeks by an independent assessor. The duration of exercise was assessed by hour per week. (Appendix VII).

1. Medication Utilization During the Study Period

The use of pharmacological interventions for participants was assessed at baseline, 4 weeks, and 8 weeks.

**Methodology:**

1. Study Design

A randomized, double-blinded, controlled, parallel group, repeated-measures design will be used. Ethical approval will be obtained from The Hong Kong Polytechnic University and Caritas Institute of Higher Education. The trial will be conducted in accordance with the Declaration of Helsinki.

1. Study subjects

Based on the effect sizes from previous relevant studies, the sample size has been calculated and 90 patients with KOA will be recruited from the general public with the physiotherapy referral from a doctor with the diagnosis of KOA and screened by knee X-ray with the Kellgren and Lawrence (KL) scale (Petersoon et al., 1997). Their age, gender, body mass index (BMI), unilateral or bilateral knees involved, duration of knee pain and any history of knee injury will be recorded as baseline information. The current study targets in mild to moderate degenerative KOA with XR showing with the KL scale (Petersoon et al., 1997) grade I and grade III (which is most beneficial to conservative treatment) (Appendix III). KL scale was proposed in 1957 and accepted by the WHO in 1961, it has been widely used in grading the severity of KOA (Samuel & Kanimozhi, 2019). All the classification of XR with the KL scale in this study will be done by a physiotherapist who has more than 10 years experience in musculoskeletal conditions and training in interpretation of knee XR with the classification of KL scale. All the subjects meet the inclusion criteria will be allocated by computer randomized program that will be created by a statistician who is not otherwise involved in the trial and does not participate in analysis or interpretation of the results. The allocation sequence will be concealed from the principal investigator enrolling and assessing participants as each participant’s allocation which will be contained in sequentially numbered sealed and stapled opaque envelopes. All the eligible subjects will be allocated into G1, G2, and G3. Each group will recruit 30 subjects. The assessor will be blinded to the patient’s treatment group assignment at all time and will carry all the baseline, 4-week and 8-week evaluations.

Inclusion criteria were based on previous relevant studies (Itoh et al., 2008; Sánchez-Romero et al., 2018). Inclusion criteria were as follows: 1) >50 to 80 years old, 2) referred with a diagnosis of KOA (i.e., primary KOA fulfilling the American College of Rheumatology criteria developed by Altman et al. (1986) (at least three out of six) for clinical and radiographical diagnostic KOA 3) presenting with anterior and/or medial knee pain with 2-3 local tender spots, 4) crepitus, 5) functional limitations caused by KOA over a period of at least six months, 6) stiffness <30 minutes, 7) KL scale (Petersson et al.,1997) of grade I to grade III; and 8) able to read Chinese and communicate in Cantonese based on literacy.

Exclusion criteria, made with reference to previous studies (Itoh et al., 2008; Sánchez-Romero et al., 2018), were: 1) having knee pain less than 6 months; 2) having other musculoskeletal diseases associated with knee pain (e.g., referred pain from the low back or posterior or lateral knee pain or co-existing pain over the other limb); 2) suffering from acute inflammation, diffuse tenderness upon palpation test, bone marrow lesion, severe joint deformity with X-rays revealing a grade IV in the KL scale (Petersson et al., 1997), coagulation disorders, metabolic, or neuropathic arthropathies, immunosuppressed or systematic disease; 3) having severe concomitant illness that might affect the clinical outcomes of this study, 4) contraindications to DN including pregnancy, malignancy, fear of DN; 5) having recent treatment involving acupuncture or DN therapy or non-pharmacological intervention (e.g., physiotherapy) within a month prior to the start of the study; 6) inability to answer questionnaires and non-responsiveness towards the assessor; 7) having a wound or pressure sore or skin problems or skin allergy, including an allergy to iodine; and 8) having a history of injecting steroids.

Participants will be provided with written information sheets and verbal explanations. Written consent will be signed. They can withdraw from the study at any time. All the adverse effects, if any, will be recorded and reported in this study. The group allocation and data will be concealed in a password-protected computer file only accessible by the principal investigator.

Table 1: Participants flow chart:

Recruit from advertisements on social media and assessed by orthopedic surgeon for eligibility of KOA

Assessed for eligibility with inclusion and exclusion criteria

Obtaining written consent

Randomized with computer program by an independent statistician and the allocation sequence will be concealed with sealed and stapled opaque envelopes

Baseline assessment

G2

DN with placebo US-guide+

supervised exercise, exercise pamphlet and educational video

G1

DN + real US-guide+ routine supervised exercise and exercise pamphlet, educational video

G3

Control from waiting list without any treatment

Follow up immediate after the last session at the 4-week and 8-week follow-ups, and data analysis and post intervention analysis with mixed model ANOVA

1. Sample Size and rational for calculation

The effect size is calculated by using G-Power version 3.1.9.4 (Franz Faul, Universität Kiel, Germany)

With reference previous similar study of using acupuncture on KOA (Williamson et al., 2007), the effect size of VAS is set as 0.339 for the VAS, power as 0.8, level of statistical significance as 0.05. The number of subjects estimated for each group will be 26; total number of subjects was 78.

1. Method of data analysis:

Statistical analyses will be performed on the Intention to treat (ITT) population, including all randomized participants. Missing data will be replaced using multiple imputation (5 iterations). Intention to treat (ITT) analysis will be used in the data analysis. The data will be analyzed by using mixed model analysis of variance (ANOVA) (two-tailed) with ‘time’ as the within subjects factor (Baseline, 4 weeks and 8 weeks after treatment), whereas the ‘group’ factor will be analyzed for the between groups differences (G1, G2 and G3). The significant level will be set at 0.05 and bonferroni correction will be applied. Wilks’ Lambda will be used for statistic significance analysis. The assumption of sphericity will be tested by the Mauchly’s test and the assumption of normality will be tested by the Shapiro-Wilk test. Post hoc analysis by will be conducted if significant difference is found in the corresponding outcomes measures so as to identify the difference amongst the comparisons between groups. All statistical analysis will be conducted using SPSS version 23 (IMB, SPSS) and all analyses will be processed blind to identify of treatment groups by an independent research assistant.

1. Details of procedure of applying US-guided DN

After taking the baseline information and randomized into 3 groups (G1, G2 & G3). Subjects in G1 will receive needling and real US scanning, and routine exercise training and education of knee care for 4 weeks and once per week while subjects in G2 will receive DN with placebo US scanning, and routine exercise training and education of knee care for 4 weeks and once per week. Subjects in G3 will be measured all the outcomes at the baseline, at the 4-week and 8-week follow-ups. For G1, the US scanning procedure is done with the subject lies on a bed with pillow in a supine position, and with knee joint supported by a towel in an around 30 degrees flexed position (Appendix VI). For G1, the physiotherapist who received special training for US scanning procedure together with the DN intervention in the Hong Kong Polytechnic University will conduct the US scanning. An US machine with high frequency (4-12MHz) linear probe [Proble Model: L12-4 broadband linear array; US Machine: Philips Lumify US system [Koninklijke Philips N.V., Eindhoven, The Netherlands] is used to assess any sign of tendinopathy over the patello-femoral and medial patello-tibial compartments (Sengupta et al., 2006) with following characteristics: mucoid degenerative changes, heterogeneity or thickening of ligaments, osteophytes, meniscus tear, hyaline cartilage thinning in trochlear cartilage defects with reference to the Outcome Measures in Rheumatology (OMERACT) US Task Force on knee OA (Bruyn et al., 2014). To avoid anisotropy, there are two views that should be used included long axis and short axis to confirm pathology (Jacobson, 2018). With integration to detail physical examination, a physical diagnosis will be made. US-guided DN will be applied to the pathological structures e.g. tendinopathy over the patella-femoral and medial patella-tibial compartments. It is a tailor-made treatment and it will last for 15 minutes and the number of needling depending on the subject’s condition. The maximum of sterile needles with the size of Dongbang Acupuncture Needles at 0.3 x 40 mm [Dong Bang Acupuncture, Inc., Marsh Barton, Exeter, United Kingdom] will be seven or below (Chung & Binkley, 2010). The number of needles used will be recorded for analysis. The procedure was performed by the physiotherapist with sterile technique by disinfecting the US probe with a wet towel [Clinell Universal Wipes, GAMA Healthcare Ltd, Hemel Hempstead, Hertfordshire], covered it with a tegaderm[3M; St. Paul, MN, USA], and used Aquasonic sterile transmission gel [Aquasonic sterile transmission gel; Parker Laboratories, INC] for the transmission of US energy to the subject. The subject’s skin will be disinfected with Betadine antiseptic solution [Mundipharma Pharmaceuticals LTD., Nicosia, Cyprus] over the targeted DN sites. Then physiotherapist will use left hand to do the US scanning and right hand will apply the DN to the target location as planned. Based on clinical experience and the procedure of DN on KOA by previous studies (Cotchett et al., 2011; Tabatabaiee et al., 2019), good response has been observed with the following protocol: the needle will be slowly moving in and out of the target muscle or tendon with the goal of eliciting an appropriate response such as a local twitching response (LTR); sensation such as a dull ache, heaviness, distension, or a reproduction of the participant’s symptoms. Then the needling will be manipulated in and out slowly every 5 minutes for 5 times to reproduce the appropriate response, and the whole treatment time will be 15 minutes. After the treatment finished, sterile gauze [A.R. Medicom Inc. (Asia) Ltd, HKSAR, China] will be applied and pressed on the side of DN. Spot tapes sterile non-stick pad [Orison TM, HKSAR, China] will be used to cover the sites received DN. The case in-charged physiotherapist will state with the subject for the whole procedure to ensure safety.

For the G2, the subject will also be positioned in a supine position same as G1. Then the physiotherapist (same therapist as in G1) will wash hand and take sterile gloves, and then do the disinfection to the skin in the target DN sites. DN will be applied to the most painful sites. To blind the patients with a placebo US-guide, the physiotherapist will do the procedure of scanning as G1 but with US monitor’s screen, out-of-view from the G2 patient’s vantage point, was turned off to blind the subjects. Then the needling will be manipulated every 5 minutes and the whole treatment time will be 15 minutes. The whole procedure similar as mentioned in G1, but there is no US scanning. After the treatment finished, sterile gauze will be applied and pressed on the side of DN. The physiotherapist will state with the subject for the whole procedure to ensure safety.

For G3, the subjects received only standardized exercise therapy and educational materials related to the care of their knees. The exercise therapy was conducted under the supervision of a registered physiotherapist weekly for 4 sessions. The exercises focused on improving knee mobility, soft tissue flexibility, muscle strength, balance and proprioception. The participants were instructed to continue the exercises at home three times per week for another four weeks.

All the outcomes will be assessed by an independent research assistant.

Details of outcomes assessment

1. The Visual Analogue Scale (VAS) is commonly used in measuring musculoskeletal pain with a 100mm horizontal line anchored with labels on top of it (Appendix 1). The reliability of the VAS for disability is moderate to good (Boonstra et al., 2008) and VAS is the most reliable tool in assessing pain as compared with numerical rating scale (NRS) and verbal rating scale (VRS), with the smallest errors in the measurement of osteoarthritis knee pain (Alghadir et al., 2018). The minimum clinically important difference (MCID) was 19.9 mm (Katz et al., 2015; Tubach et al., 2005).
2. Knee injury and Osteoarthritis Outcome Score (KOOS)-short form is validated to be used in KOA patients (Lyman et al., 2016). KOOS is a valid, reliable and responsive outcomes measure, and it can improve the validity as compared with WOMAC (Roos et al., 2003). The Chinese translated version of KOOS is a reliable and valid instrument for OAK patients and showed fairly strong association with WOMAC (Cheung, Ngai and Ho., 2016). As WOMAC requires license and cost, KOOS is free to be used, KOOS already has been commonly used as a functional outcomes in most public hospitals in Hong Kong for KOA patients. The KOOS-short form involves three domains including pain, symptoms and quality-of-life (QoL). The score from ‘0’ to ‘4’ indicated none to severe and then the KOOS pain score can be calculated with the following formula:

KOOS-pain= 100 – (mean score of pain domain x 100)/4

The values of KOOS-subscales (symptoms and QoL) can be assessed by the above formula.

1. Evaluation of the Validity of placebo method

This study involves US-guide and stated clearly in the consent form and information sheet provided to very subjects. If one the study group does not provide US-guide, they may know that they are not allocated into the intervention group. To avoid the bias and potential placebo effect from US-guide, it is necessary to blind the subjects during the procedure of US-guide DN. All the subjects in G1 and G2 will receive either real-US-guide or placebo US-guide with US monitor’s screen, out-of-view from the G2 patient’s vantage point, was turned off to blind the subjects.

To ensure it, all the subjects in G1 and G2 will be asked whether they are receiving a real US-guide or a placebo US-guide DN. Is placebo US-guide really effective to service the purpose of blinding the subjects? Then the data will be collected for analysis by Chi-squared test for the nominal data with using SPSS version 23 (IMB, SPSS) and an alpha is set at 0.05.

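### The protocol describes the control arm (G3) both as untreated and as receiving supervised exercise with education, so the comparisons with G3 have two possible meanings

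*Protocol*

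**What the plan says.** The protocol describes the control arm in five places.

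- **Purpose of the project:** "Control group will be used to compare the effects of routine exercise therapy".
- **Background, last paragraph:** the control is there to "contrast the condition of natural healing with routine exercise and knee care against the interventions of DN", with and without ultrasound guidance.
- **Methodology, Table 1 (participants flow chart):** the G3 box reads "Control from waiting list without any treatment". The G1 and G2 boxes in the same chart list supervised exercise, a pamphlet and an educational video besides needling.
- **Methodology, details of procedure, opening paragraph:** G1 and G2 each get needling together with "routine exercise training and education of knee care for 4 weeks and once per week". For G3 it says only "Subjects in G3 will be measured all the outcomes at the baseline, at the 4-week and 8-week follow-ups".
- **Methodology, details of procedure, G3 paragraph:** "For G3, the subjects received only standardized exercise therapy and educational materials related to the care of their knees". It continues "The exercise therapy was conducted under the supervision of a registered physiotherapist weekly for 4 sessions", and ends "The participants were instructed to continue the exercises at home three times per week for another four weeks".

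G3 enters both null hypotheses and is one of the three levels of the group factor in the mixed-model ANOVA.

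**The concern.** An arm that receives nothing cannot also receive four supervised exercise sessions and education. The two descriptions make G3 a different comparator, and the comparator decides what a difference from G3 means.

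If G3 exercises, a benefit of G1 or G2 over G3 is credited to needling on top of a shared exercise programme. If G3 is untreated, the same benefit could come from needling, exercise, education or any mixture, and the trial could not tell them apart. That would not serve the stated purpose of using the control to compare the effects of routine exercise.

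A second, smaller question concerns weeks 4 to 8. The home-exercise instruction stands in the G3 paragraph and is not repeated for G1 or G2, so the protocol does not make clear whether exercise is meant to be the same in all arms at the 8-week assessment.

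**Working it through.** This point rests on text, and the plan has no figure for it to reproduce. The sample-size paragraph gives one VAS effect size, 0.339, but does not say which contrast between arms it represents, so it does not help to settle what G3 is.

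**Step 1. What each place says about G3**

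| Place in protocol | Exercise for G3? | Education for G3? |
|---|---|---|
| Purpose of the project | Yes | Not mentioned |
| Background | Yes | Knee care, yes |
| Table 1 flow chart | No (untreated) | No (untreated) |
| Procedure, opening paragraph | Silent | Silent |
| Procedure, G3 paragraph | Yes, supervised weekly, 4 sessions | Yes |

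Three places give G3 exercise, one gives it nothing, and one does not say. No sentence ranks these places.

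**Step 2. What the contrasts estimate**

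For bookkeeping only, write N for needling, U for real rather than placebo ultrasound guidance, and E for exercise with education, as if the effects added. Then G1 = N + U + E and G2 = N + E.

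| Contrast | G3 exercises (G3 = E) | G3 untreated (G3 = 0) |
|---|---|---|
| G1 - G3 | N + U | N + U + E |
| G2 - G3 | N | N + E |
| G1 - G2 | U | U |

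The two readings differ by the whole of E in both contrasts with G3. The G1 - G2 row is the same under either reading.

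**Step 3. How much of the analysis is involved**

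Three arms give three pairs, and two of the three include G3. This applies to VAS and to the KOOS short form. The three-group tests also depend on the choice, because G3 is one of the three groups.

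**Step 4. Weeks 4 to 8**

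Let H be the effect of the home programme: 3 sessions a week x 4 weeks = 12 sessions. Take the reading in which G3 exercises.

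- If the instruction covers all arms, H cancels, and the 8-week contrasts remain N + U and N.
- If it covers G3 only, they become N + U - H and N - H.

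The G3 paragraph refers to the participants without naming an arm. The G1 and G2 text describes four weekly sessions and does not say what follows.

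**The case against.** The strongest reply is that the two readings are not evenly balanced. The procedure paragraph is the operative text and specifies supervision, frequency and content. The Purpose and Background sections agree with it. Exercise compliance is to be assessed at 4 and 8 weeks with no arm exempted. The flow chart also times follow-up from the last session, which an untreated arm would not have. On this view one chart box is wrong, perhaps because no treatment was loosely meant as no needling.

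Most of that stands. The text leans towards an exercising control, and the chart box is the outlier. It does not remove the problem. The box expressly denies any treatment, beside boxes that list exercise for the other two arms, and no passage says that the procedure text overrides it. The suggested loose meaning is an inference.

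A reader might draw four stronger conclusions that the documents do not support:

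- *The opening procedure paragraph is a second contradiction.* It is only silent on treatment for G3, and the G3 regimen follows later in the same section.
- *G3 is shown to exercise more than G1 and G2 after week 4.* The protocol never says that G1 and G2 stop. Both have the pamphlet and video, and exercise hours are recorded at 8 weeks for participants generally. This is an ambiguity and not a demonstrated imbalance.
- *Exercise compliance would be meaningless in an untreated arm.* It is recorded as hours per week, which can be measured in anyone. Only adherence to a prescribed programme would lose its sense.
- *The distortion can be expressed as a share of the 19.9 mm clinically important difference.* The protocol gives no estimate of the exercise effect, so any such share would be a guess.

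**Conclusion.** The contradiction is real and unresolved, and it concerns what an arm receives, which belongs in the protocol. It leaves the meaning of two of the three pairwise comparisons, and of the three-group tests, undetermined on both primary outcomes. The undetermined amount is the full effect of supervised exercise with education, whose size the documents do not give. G1 versus G2, the comparison of real with placebo guidance, is unaffected.

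One might infer that the G3 contrasts can never be interpreted. That goes too far: they can be interpreted once the control condition is fixed or, after the event, once what was delivered is documented. The 8-week contrasts with G3 would also differ in exercise if the home programme applies to G3 alone, but the text does not establish that it does.

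The conclusion assumes only that both descriptions of G3 are current text. The additive notation serves to show which components cancel; the finding does not rest on additivity.

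**What to change.** 1. Reconcile the G3 box in Table 1 with the Purpose, the Background and both procedure paragraphs, so that one control condition is stated throughout. Which regimen is intended is for the investigator to say.
2. State in identical words for G1, G2 and G3 which exercise and education components apply in weeks 0-4 and in weeks 4-8, including whether the home programme applies to every arm.
3. Word the G3 conclusion to match: an add-on effect of needling if G3 receives the same exercise and education, or a package against no treatment if it does not.
4. The protocol mixes future and past tense, so recruitment status cannot be told from it. If randomisation has begun or finished, record what G3 participants actually received before interpreting any contrast with G3.

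The cost is protocol wording and one flow chart box. No participants, visits or measurements are added.

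### G3 is an untreated waiting list in the flow chart but a supervised exercise arm in the procedure text, so G1-G3 and G2-G3 can each mean two different contrasts

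*Protocol*

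**What the plan says.** The protocol describes G3 in five places.

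- **Participants flow chart (Table 1, Methodology).** The G3 box reads "Control from waiting list without any treatment". The G1 box beside it reads "DN + real US-guide+ routine supervised exercise and exercise pamphlet, educational video", and the G2 box also lists supervised exercise, a pamphlet and a video.
- **Procedure text, opening paragraph (Methodology).** Weekly exercise training and knee-care education over four weeks are named for G1 and again for G2. For G3 the paragraph says: "Subjects in G3 will be measured all the outcomes at the baseline, at the 4-week and 8-week follow-ups". It does not say what treatment, if any, G3 has.
- **Procedure text, G3 paragraph (Methodology).** Here "the subjects received only standardized exercise therapy and educational materials related to the care of their knees", and "The exercise therapy was conducted under the supervision of a registered physiotherapist weekly for 4 sessions".
- **Purpose of the project.** "Control group will be used to compare the effects of routine exercise therapy".
- **Background.** The study is to include a "control group to contrast the condition of natural healing with routine exercise and knee care".

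Both null hypotheses refer to G3, and the planned mixed model ANOVA has group as a three-level factor (G1, G2, G3).

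**The concern.** The flow chart and the G3 paragraph describe the same arm over the same four weeks, and they cannot both be true. A site working from the flow chart would leave G3 untreated. A site working from the procedure text would bring G3 in each week for supervised exercise. These are two different trials.

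What is at stake is attribution. If G3 is untreated, a better result in G2 than in G3 could come entirely from the exercise and education that G2 also receives, and it could not be credited to needling. If G3 exercises, the same result is evidence on what needling adds to that background. The same holds for G1 against G3, and the overall three-group test inherits the ambiguity because G3 is one of its levels.

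**Working it through.** The point is a conflict of text, and the plan attaches no figure to it. The sample size statement (effect size 0.339, 26 per group, 78 in total) does not say which comparison the effect size represents, so it cannot show which control was intended. The check is therefore to set the descriptions side by side and follow them into the contrasts.

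**Step 1: what each arm receives in the treatment period.**

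| Place in protocol | G1 | G2 | G3 |
| --- | --- | --- | --- |
| Flow chart | needling, real guidance, exercise, education | needling, placebo guidance, exercise, education | no treatment |
| Procedure text, opening | needling, real guidance, exercise, education | needling, placebo guidance, exercise, education | treatment not stated |
| Procedure text, G3 paragraph | – | – | supervised exercise, education |
| Purpose | – | – | routine exercise |
| Background | – | – | natural healing with routine exercise and knee care |

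The G1 and G2 columns are consistent throughout. In the G3 column the flow chart stands against the G3 paragraph, the purpose and the background. The opening of the procedure text is silent.

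**Step 2: can the flow chart label mean only that G3 has no needling?** The G1 and G2 boxes in the same chart list exercise and educational material as part of what those arms receive. The G3 box lists neither and excludes any treatment. Within the chart, exercise counts as treatment, so this reading does not work.

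**Step 3: effect on the contrasts.** Write m1 and m2 for the mean outcomes in G1 and G2, which are the same under either description. Write m3(none) for the G3 mean if untreated and m3(ex) for the G3 mean with exercise and education.

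- G1-G2: m1 − m2 under both readings, so unchanged.
- G2-G3: m2 − m3(none) or m2 − m3(ex).
- G1-G3: m1 − m3(none) or m1 − m3(ex).

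For G1-G3 and G2-G3 alike, the difference between the readings is

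[m − m3(none)] − [m − m3(ex)] = m3(ex) − m3(none),

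where m is m1 or m2. That is the full effect of the exercise and education package given without needling. No assumption that treatment effects add up is needed. The protocol gives no value for this quantity, so it cannot be expressed in millimetres on the VAS or in KOOS points from the document.

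**Step 4: count.** Of the three pairwise comparisons, two (G1-G3 and G2-G3) change meaning and one (G1-G2) does not. This applies to pain and to function.

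**The case against.** The strongest reply is that the flow chart box is a single leftover. The purpose, the background and the detailed G3 paragraph all describe a control with exercise, and a reader who takes the document as a whole would probably settle on that. This stands as a description of where the inconsistency lies, and it means the repair is likely to be small. It does not remove the conflict: the flow chart is current text, it is explicit, and no sentence overrides it. The past tense of the G3 paragraph might suggest a record of what was actually done, but the protocol also uses the past tense for eligibility criteria and for the placebo scanning, so the tense settles nothing.

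Several stronger readings are tempting and are not supported.

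- *The waiting list is a separate source of patients.* The flow chart places G3 after consent, randomisation and baseline assessment. The paragraph on study subjects and the opening of the procedure text both allocate eligible subjects at random to all three groups.
- *The opening of the procedure text is a second statement that G3 is untreated.* It says that G3 is measured, not that it is only measured. It is incomplete and does not itself contradict the G3 paragraph.
- *The Benefits section makes a claim that an untreated control would undermine.* Its sentence about enhancing needling with exercise concerns what ultrasound guidance adds. That is G1-G2, which is unaffected.
- *Exercise compliance could not be measured in an untreated arm.* The outcome is recorded as hours per week, which can be collected from anyone.

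**Conclusion.** The protocol contradicts itself on what G3 receives, and this must be corrected. The consequence is confined to G1-G3 and G2-G3 and to the overall group test that contains them. The G1-G2 comparison, which isolates real against placebo guidance, keeps its meaning, so a reader should not infer that the trial as a whole is uninterpretable.

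The size is structural: two of the three pairwise comparisons, for both primary outcomes, differ between the readings by the entire effect of exercise and education. A reader might want to set that effect against the stated minimum clinically important difference of 19.9 mm, but any such fraction would rest on an assumed exercise effect, and the conclusion does not need one. The conclusion assumes only that the flow chart and the procedure text are both in force, as they appear to be. It takes no position on which control is the right one.

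**What to change.** 1. Reconcile the flow chart with the purpose, the background and the G3 paragraph of the procedure text, so that all give one definition of what G3 receives. The choice is for the sponsor and investigator.
2. State that definition in the opening paragraph of the procedure text as well, where treatment is now named for G1 and G2 but not for G3.
3. Limit the conclusions drawn from G1-G3 and G2-G3 to the contrast that the definition supports: either needling added to exercise and education, or needling with exercise and education against no treatment.
4. If patients are already enrolled, report what G3 patients actually received. The data collection form already has an exercise-compliance entry to start from.

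The cost is protocol wording and a corrected flow chart, plus a short descriptive report if item 4 applies. No extra patients or visits are needed.
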